## Abstract

**Background:**

Breast cancer ranks first in women, and is the second cause of death in this gender. In addition to genetics, the environment contributes to the development of the disease, although the factors involved are not well known. Among the latter is the influence of microorganisms and, therefore, attention is recently being paid to the mammary microbiota. We hypothesize that the risk of breast cancer could be associated with the composition and functionality of the mammary/gut microbiota, and that exposure to environmental contaminants (endocrine disruptors, EDCs) might contribute to alter these microbiota.

**Methods:**

We describe a case-control clinical study that will be performed in women between 25 and 70 years of age. Cases will be women diagnosed and surgically intervened of breast cancer (stages I and II). Women with antecedents of cancer or advanced tumor stage (metastasis), or who have received antibiotic treatment within a period of 3 months prior to recruitment, or any neoadjuvant therapy, will be excluded. Controls will be women surgically intervened of breast augmentation or reduction. Women with oncological, gynecological or endocrine history, and those who have received antibiotic treatment within a period of 3 months prior to recruitment will also be excluded. Blood, urine, breast tissue and stool samples will be collected. Data regarding anthropometric, sociodemographic, reproductive history, tumor features and dietary habits will be gathered.

Metabolomic studies will be carried out in stool and breast tissue samples. Metagenomic studies will also be performed in stool and breast tissue samples to ascertain the viral, fungal, bacterial and archaea populations of the microbiota. Quantitation of estrogens, estrogen metabolites and EDCs in samples of serum, urine and breast tissue will also be performed.

**Discussion:**

This is the first time that the contribution of bacteria, archaea, viruses and fungi together with their alteration by environmental contaminants to the risk of breast cancer will be evaluated in the same study. Results obtained could contribute to elucidate risk factors, improve the prognosis, as well as to propose novel intervention studies in this disease.

**Trial registration:**

ClinicalTrials.gov NCT03885648, 03/25/2019. Retrospectively registered.

## Trial status

The trial is currently in progress. Enrolment of patients and analysis of data continues.

## Background

Humans are colonized by commensal microorganisms, which form the human microbiota. The community of microorganisms that exist within the gastrointestinal (GI) ecosystem is termed gut microbiota [1]. The GI microbiota is mainly composed by up to 10^14^ bacteria and several archaea, eukaryotes and virus [2]. In fact, humans are thought be in involved in a symbiotic relationship with the gut microbiota [3]. In human health, the function of the GI microbiota is to keep a dynamic equilibrium with the host, playing both local and remote roles [4] in important physiological processes, particularly inflammation and the immune response [2]. This interspecies balance is named eubiosis [5]. However, a “disequilibrium” in the microbiota (referred to as dysbiosis) may lead to several human diseases [4].

Given that the gastrointestinal tract is a complex, open, and integrated ecosystem with the external environment [5], exposure to external insults (i.e. pesticides and many other pollutants) may lead to dysbiosis. Failures of host barriers, defects in the immune system, and loss of eubiosis have been proposed to explain the potential impact of gut microbiota on carcinogenesis [6]. Moreover, it has been suggested that changes in the microbiota may even promote the development of extra-intestinal tumors [4] and be involved in its aggressiveness [7]. Recent findings revealing gut microbiota variations in patients with benign compared with malignant tumors suggest that the microbiome profile could be associated with cancerous state of the tumor [7].

Breast cancer ranks first and is the second cause of death in women [8]. In addition to genetics, environmental factors such as the influence of microorganisms could have a role in the development and progression of this disease [9, 10].

Although human breast tissue was previously presumed to be sterile, high-throughput technologies revealed a microbiome profile that has recently been characterized [7]. Furthermore, the local breast microbiota seems to differ in women with and without breast cancer [10].

Concerning the influence of microbes on breast cancer, some studies have focused on viruses. Up to 50% of breast tumors are Epstein-Barr positive [11], and human papilloma virus also appears to be associated with breast cancer [12]. In addition, the diversity and composition of the gut microbiota may affect breast cancer risk through the modulation of systemic levels of estrogens and inflammation [13]. In this sense, alterations of microbes able to metabolize estrogens and other endogenous hormones lead to an increment in circulating estrogen levels, which ultimately increase the risk of breast cancer development [14]. Furthermore, a reduced abundance of *Methylobacterium* in breast cancer patients has been correlated with tumors of greater invasive potential [15]. Moreover, exposure to a wide variety of xenobiotics (i.e. endocrine disruptors compounds (EDCs), which are found in routinely used products, lead to an increment of the risk of breast cancer [9]. Indeed, it has been hypothesized that in utero exposure to EDCs plays a role in breast cancer in women later in life [16]. Altogether, this background has drawn the attention of the scientific community in the mammary microbiome direction, albeit studies are still very limited and some of the published results are contradictory [17].

The rationale of our work is that the risk of breast cancer could be associated with the composition and functionality of the mammary/gut microbiota, and that exposure to environmental contaminants (i.e. EDCs) might contribute to alter both the gastrointestinal and mammary microbiota. Consequently, we aim to decipher the correlation among i) the composition of both the mammary and the gut microbiota, ii) the metabolic pathways in which they are involved, iii) the role of EDCs exposure to its alteration, and iv) the risk and progression of breast cancer, which might have broad implications in the prevention, diagnosis, treatment and prognosis of this disease.

## Methods/design

The study will follow the Declaration of Helsinki (52nd General Assembly, Edinburgh, Scotland, October 2000) and the Spaniard legislation regarding clinical research: Normas de Buena Práctica Clínica y Ley de Investigación Biomédica Real Decreto 561/1993 y 033/2004. All data obtained will be confidential and only the researchers and participants, upon request, will have access to them. The study will also follow the data protection legislation of Spain (Ley Orgánica de Protección de Datos de Carácter Permanente, Ley 15/1999 de 13 de Diciembre de 1999) to guarantee data confidentiality, treatment and availability for the participants.

Participation in the study is volunteer. Participants will be informed about the nature of the research and the usage of biological samples as well as the obtained data. In addition to verbal information, participants will be presented and read an informed consent. Permission has been granted by the Ethics Committee of Andalusia (Comité de Ética de la Investigación Biomédica de Andalucía, Spain).

### Study subjects

#### Inclusion and exclusion criteria

In this ongoing case-control study, already registered in ClinicalTrials.gov (Identifier NCT03885648), women’s age will range 25–70 years. Cases will be defined as women diagnosed and surgically intervened of incident breast cancer, stages I and II. Controls will be women surgically intervened of breast augmentation or reduction. Women with antecedents of cancer or advanced tumor stage (metastasis), or who have received antibiotic treatment within a period of 3 months prior to recruitment, or any neoadjuvant therapy, will be excluded of the study. Women with oncological, gynecological or endocrine antecedents and those who have received antibiotic treatment within a period of 3 months prior to recruitment will be also excluded. Controls will be matched to cases by age (± 2 years), category of body mass index and hospital of recruitment.

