#### Biological samples

Blood, breast tissue, stool and urine samples from cases and controls will be collected. Cases women will be enrolled on the same day of the diagnosis. They will be informed about the goals and procedures of the study and their participation will be requested, and those who accept to participate in the study will sign the informed consent. They will be supplied with a kit containing: 1 thermal bag, 1 freezer block, 1 pair of latex gloves, 1 disposable bedpan, 1 spatula, and 2 disposable plastic containers for urine and stool samples.

The day of the surgery, a blood sample will be taken. Serum will be separated by centrifugation to carry out a thorough biochemical analysis and determine estrogens. Breast tissue samples will be taken during surgery, from a marginal area 3–5 cm apart from the tumor. For controls, samples will be taken from any available breast tissue during breast reduction or augmentation surgery. Both feces and urine samples, from healthy and breast cancer-affected women will be collected the day previous to mammary surgery.

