## Discussion

There are 7 studies registered in ClinicalTrials.gov dealing with breast cancer and microbiota, 2 already completed and 4 currently ongoing. Of the 2 completed studies, one investigated the antibiotic profilaxis in oncological surgery of the breast, and the other investigated the relationship between intestinal bacteria and breast cancer risk. As for the studies in progress, these are trials investigating various intervention strategies (probiotics, physical activity, diet), the effects of gut microbiome on the neoadjuvant chemotherapy-induced immunosurveillance in triple negative breast cancer, or the effects of chemotherapy on gut bacteria in newly diagnosed breast cancer. Our study is a case-control clinical trial that aims at ascertaining the connection relating i) the composition of both gut and breast microbiota, ii) the functionality of both gut and breast microbiota, and iii) the exposure to environmental contaminants with the risk of developing breast cancer. To the best of our knowledge, it is the first study undertaking the simultaneous analysis of the microbiota of the mammary tissue and the intestine, and also the first attempt to link the microbiome with the EDC load and the risk of this disease.

The microbiota is affected by either modifiable and unmodifiable factors such as genetics, stress, diet, physical activity, lactation, delivery mode, antibiotic treatment, smoking, age, and alcohol consumption, among others [36]. For this reason, in an attempt to control some of the modifiable factors, all participants will answer three questionnaires to record their sociodemographic data, adherence to the Mediterranean diet, and frequency of food consumption. For the same reason, we set stringent inclusion and exclusion criteria. Women participating in the study will be newly diagnosed cases of breast cancer. Therefore, women with antecedents of cancer or advanced tumor stage will not take part, nor those who have received antibiotic treatment 3 months prior to recruitment, or any neoadjuvant therapy. Likewise, regarding the controls, women with oncological, gynecological or endocrine antecedents and those who have received antibiotic treatment 3 months prior to recruitment will not be included.

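### The 3-month antibiotic exclusion is counted back from recruitment, not from sampling, so it does not guarantee an antibiotic-free period when stool and breast tissue are taken

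*Protocol article*

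**What the plan says.** Under Inclusion and exclusion criteria, the article excludes women "who have received antibiotic treatment within a period of 3 months prior to recruitment". A second sentence there, whose exclusion list the Discussion assigns to the controls, uses the same reference date: "those who have received antibiotic treatment within a period of 3 months prior to recruitment will be also excluded". The Methods paragraph of the abstract and the Discussion ("nor those who have received antibiotic treatment 3 months prior to recruitment, or any neoadjuvant therapy") repeat it, so the choice of date is consistent and not a slip in one place.

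The section Biological samples sets the other dates:

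- Enrolment of cases: "Cases women will be enrolled on the same day of the diagnosis". No enrolment day is given for controls.
- Stool, both groups: "Both feces and urine samples, from healthy and breast cancer-affected women will be collected the day previous to mammary surgery".
- Breast tissue, cases: "Breast tissue samples will be taken during surgery".
- Breast tissue, controls: "samples will be taken from any available breast tissue during breast reduction or augmentation surgery".

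Stool and breast tissue are the two materials in which the microbiota is measured (Breast and intestinal microbiota). The Discussion lists antibiotic treatment among the factors that affect the microbiota and gives that influence as the reason for strict eligibility criteria.

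**The concern.** The antibiotic criterion is there to protect the microbiota measurement, so the date that matters is the date of sampling. The plan ties the criterion to an earlier date. Between the two lies the interval from enrolment to surgery, whose length is not stated and during which no antibiotic rule applies. The exposures that slip through are, by construction, the ones closest in time to the sample.

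The stool and breast tissue results feed the Mann-Whitney and PERMANOVA comparisons and the metabolomics. The breast tissue is also cultured for the DNA-damage assay. Antibiotic effects in some women would add noise to these comparisons. If exposure happened to be more frequent in one group, they would also confound the case-control contrast. The analysis could not correct for this, because antibiotic use in the interval is not among the listed covariates.

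**Working it through.** There is no figure in the plan to reproduce, so the first check is a timeline.

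**Timeline.** Let day 0 be enrolment and g the number of days from enrolment to surgery (not given). The rule screens the 3 months that end on day 0. Stool is taken on day g - 1 and tissue on day g. The unscreened period is then g - 1 days before stool and g days before tissue. Taking 3 months as 90 days, the part of the 90 days before stool that the rule still covers is 90 - (g - 1). The values of g are illustrative:

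| g (assumed) | Unscreened before stool | Unscreened before tissue | Screened part of the 90 days before stool |
|---|---|---|---|
| 7 days | 6 days | 7 days | 84 days |
| 30 days | 29 days | 30 days | 61 days |
| 60 days | 59 days | 60 days | 31 days |

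For any g above 1 day, the antibiotic-free time that the criterion guarantees at sampling is zero, because a course begun after enrolment and still running at sampling violates nothing that is written. For short g, however, most of the relevant 3 months is still covered.

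**Is there a rule elsewhere?** The section Other sources of information and covariables lists anthropometric, sociodemographic, reproductive, tumour and dietary items, and antibiotic use is not among them. Participants grant access to their clinical history, but no stated rule acts on what it shows. The section Statistical analysis has no provision for antibiotic exposure.

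**Possible size.** Assume a monthly probability r of taking an antibiotic, constant and independent between months, with r = 0.03 to 0.05. Neither r nor the gap m (in months) comes from the article. The share of a group exposed in the gap is 1 - (1 - r)^m:

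- m = 7/30: 1 - 0.97^0.233 = 0.7%; 1 - 0.95^0.233 = 1.2%.
- m = 1: 3% to 5%.
- m = 3: 1 - 0.97^3 = 8.7%; 1 - 0.95^3 = 14.3%.

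With 100 women per group, that is about 1 woman, 3 to 5 women, or 9 to 14 women.

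**Cost if whole pairs are dropped.** If both groups had the same gap and exposure were independent within a pair, the share of pairs with at least one exposed woman would be 1 - (1 - r)^(2m). That is 5.9% to 9.8% for 1 month and 16.7% to 26.5% for 3 months.

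**The case against.** The strongest reply is that eligibility seems to run past enrolment. The same sentence excludes women with any neoadjuvant therapy, which can hardly take effect unless status is looked at again up to surgery, and cases are defined as women who have been both diagnosed and operated on. With access to the clinical history as well, the full protocol may have antibiotic use reconfirmed at sampling, a step that an article often leaves out. This makes it possible that exposed women are caught in practice. It does not supply an antibiotic rule: the neoadjuvant exclusion carries no recruitment date, whereas the antibiotic window carries one everywhere it appears.

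The second reply is that the size is unknown and may be trivial. That stands. With a gap of about a week, roughly one woman per hundred would be affected under the assumed rates.

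The third concerns imbalance. A reader might infer that cases and controls wait for different times and hence differ in exposure, by something like 10 percentage points. The documents do not support this. Both groups have the same window and the same sampling days, and the only opening is that control enrolment timing is not stated. Under the assumed rates, a wait of 3 months against 1 month gives a difference of 5.7 to 9.3 points and 3 months against none gives 8.7 to 14.3, but both the rates and the waits are invented inputs.

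**Conclusion.** The mismatch of dates is established from the article's own text: the exclusion window ends at recruitment, the microbiota samples are taken around surgery, and no stated provision covers the time between. The criterion as written does not secure an antibiotic-free period at sampling.

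Its consequence is not established. The affected share runs from about 1% to 9-14% of a group over gaps of 1 week to 3 months, and this rests wholly on an assumed use of 3-5% per month. Whether it differs by case status cannot be told. It would also go too far to say that the criterion is defeated, since it still removes every woman exposed in the 3 months before recruitment. Nor do the documents show that any exposed woman has in fact been analysed. This is a gap in the rule that should be closed, with an effect of unknown size.

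**What to change.** 1. Count the same 3-month window back from stool collection, in cases and controls alike.
2. Ask about antibiotic use again when the stool and urine kit is handed in. For women already enrolled, check the clinical history to which they have granted access. The article says that enrolment continues, so the change can still help.
3. Leave women exposed in that window out of the microbiota analyses, or at the least repeat those analyses without them as a sensitivity analysis.
4. Record separately any antibiotic given between stool collection and tissue sampling. Handle it as a covariate or in a sensitivity analysis for breast tissue, not as an exclusion. A window run literally up to the tissue sample would remove every woman given an antibiotic on the day of surgery. The article does not mention such use, and the change proposed here concerns only its recording and analysis.
5. State the enrolment day for controls, so that the gap can be compared between groups.

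If the full protocol already reconfirms antibiotic status at sampling, it is enough to say so and give the reference date. Otherwise the cost is one repeated question, one revised sentence and some loss of women from the microbiota analyses. That loss is small for short gaps but could reach 9-14% of a group for 3-month gaps under the assumed rates, and more if matched partners are dropped too.

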#### Sample size

Sample size has been calculated taking into consideration the incidence of breast cancer in Spain, the female population of Andalusia and the formula described by Aguilar-Barojas (2005) [18]. Because of that, the number of breast cancer cases will include at least 100 women, matched with 100 control women subjected to breast reduction or augmentation. Three hospital centers will participate in the recruitment: The Unit of Mammary Pathology, General Surgery Service, University Hospital of Jaén, Spain; the Unit of Mammary Pathology, General Surgery Service, University Hospital Campus de la Salud, Granada, Spain; and Ana Moreno Clinic (Granada, Spain).

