### Statistical analysis

Relative abundance of the microbes will be expressed as median ± range. Differences among microbes will be calculated by the *U*-Mann de Whitney. Intestinal and mammary microbiota clusters will be calculated by an analysis of principal components made with the bioinformatic data. Those data will be normalized between 0 and 1, and the Euclidean distance will be evaluated. A permutation ANOVA (PERMANOVA) will be carried out with the PRIMER 7 software. Finally, a tree diagram will be built for each evaluated group based on the different taxonomic scales.

For metabolomic statistical analysis and data display purposes, any missing values will be assumed to be below the limits of detection, and these values will be imputed with the compound minimum (minimum value imputation). The data will be tested for variance homogeneity, and if there were unequal variances, the data will be log-transformed. The statistical analysis of the data will be performed using Array Studio (OmicSoft, NC, USA) and proprietary software from Metabolon. A t-test for equality of the means will be carried out between the intestinal and mammary microbiota and for each metabolite to determine differences. A *p*-value 0.05 will be considered statistically significant. A one-way ANOVA, assuming homogeneity of variance, will be used to determine whether at least two unknown means are all equal or at least one pair of means is different. In case that the variances were unequal, a Welch-ANOVA will be performed. The false discovery rate (q-value) will be calculated to take into account the multiple comparisons that normally occur in metabolomics-based studies, thus estimating the reliability of the results. A q-value 0.1 will be considered statistically significant.

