Random forest (RF) is a supervised classification technique based on an ensemble of decision trees [35] with several advantages. It makes no parametric assumptions, and variable selection is not needed. It does not overfit, and it is invariant to transformation. In RF analysis, it is not necessary to cross-validate or do a separate test set to obtain an unbiased estimate of the test set error. A “variable importance” measure will be computed to determine which variables (metabolites) make the largest contribution to the classification. The mean decrease in accuracy (MDA) will be used as this metric and will be determined by randomly permuting a variable, running the observed values through the trees, and then reassessing the prediction accuracy. If a variable were not significant, then this procedure will have little change in the accuracy of the class prediction (permuting random noise will give random noise). By contrast, if a variable is relevant for the classification, the prediction accuracy will drop after such a permutation, which will be recorded as the MDA. Thus, the RF analysis provides an “importance” rank ordering for biochemicals [35].

Participants will be grouped into tertiles of urinary EDC levels based on their distributions among the controls. Odds ratios and 95% confidence intervals (CIs) for breast cancer comparing the second and third tertiles with the first tertile will be estimated using logistic regression models. Further, associations of participant characteristics with urinary EDC levels, estrogens and estrogen metabolites and fecal microbiome measures will be evaluated by using general linear models and testing either for differences across categories or for trends across categories. Linear regression models will also be used to evaluate associations of each steroid measure with measures of the diversity of the fecal microbiome, abundance and with taxonomic groups at phylum and family levels, adjusting by covariates.

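### Controls are matched to cases on age, BMI category and hospital, but the stated odds-ratio model and the microbe test do not use the matching, so odds ratios may be pulled toward 1 and tests made conservative

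*Protocol article*

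**What the plan says.** **Design.** Under Inclusion and exclusion criteria: "Controls will be matched to cases by age (± 2 years), category of body mass index and hospital of recruitment". Under Sample size, the cases will be "at least 100 women, matched with 100 control women subjected to breast reduction or augmentation". The article does not use the words individual or pair, but a two-year age caliper with equal numbers is most naturally read as one-to-one individual matching.

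**Analysis.** Under Statistical analysis, three sentences bear on the point:

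- Exposure groups: "Participants will be grouped into tertiles of urinary EDC levels based on their distributions among the controls".
- Odds ratios: those "comparing the second and third tertiles with the first tertile will be estimated using logistic regression models". No conditional model, matching term or covariate is named.
- Microbes: "Differences among microbes will be calculated by the *U*-Mann de Whitney". The groups compared are not named; case versus control is the natural reading.

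The one explicit statement of covariate adjustment belongs to a later sentence, on linear regressions of steroid measures on fecal microbiome diversity, "abundance and with taxonomic groups at phylum and family levels, adjusting by covariates". It is not attached to the odds ratios. No sentence of the statistical section mentions the matching.

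**The concern.** Matching in a case-control study forces the controls to resemble the cases on the matching factors. If those factors are also related to exposure, the exposures of a case and her matched control are positively correlated. An analysis that ignores the factors then compares two groups that selection has made too alike, with two consequences: the odds ratio moves toward 1, and the model-based standard error is larger than the true sampling error, so tests reject too seldom. Matching does not control a confounder by itself; the analysis has to carry it.

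The EDC-tertile odds ratios are the only estimates of breast cancer risk that the article names, so attenuation there bears directly on the study's hypothesis. The article gives some reason to expect a link between matching factors and measurements: the Discussion lists age among the factors that affect the microbiota, and the section on EDCs in urine adjusts concentrations for creatinine partly because of body composition.

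**Working it through.** **The plan's own figure.** The only relevant number is 100 cases with 100 controls. Its basis is given as "Sample size has been calculated taking into consideration the incidence of breast cancer in Spain", the female population of Andalusia and a cited formula, with no effect size, exposure prevalence, power or correlation. It can be neither reproduced nor refuted, and it shows no allowance for matching.

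**Inputs.** From the article: 100 pairs, and tertiles cut on the controls (about 1/3 of controls in each). The significance level of 0.05 is borrowed from the metabolomics paragraph and taken as two-sided. Assumed, because the article gives no values: the true odds ratio ψ and the strength of the link between matching factors and exposure.

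**Check 1: binary exposure, 50% of controls exposed.** Let the control's exposure probability x vary between pairs as a symmetric beta distribution with within-pair correlation r. The case's probability is ψx/(1 − x + ψx). Averaging over pairs gives P, and the crude odds ratio is P/(1 − P), because the control odds are 1.

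| r | ψ = 1 | ψ = 2 | ψ = 3 |
|---|---|---|---|
| 0.1 | 1.00 | 1.87 | 2.70 |
| 0.3 | 1.00 | 1.63 | 2.17 |
| 0.5 | 1.00 | 1.41 | 1.73 |

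At r = 0.5 the result is exactly √ψ: √2 = 1.41 and √3 = 1.73.

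**Check 2: 1/3 of controls exposed, pair effect on the logit scale with standard deviation s, ψ = 2, 100 pairs.**

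| s | Crude OR | Model SE of log OR | True SE |
|---|---|---|---|
| 0 | 2.00 | 0.292 | 0.292 |
| 0.5 | 1.93 | 0.292 | 0.284 |
| 1.0 | 1.78 | 0.292 | 0.267 |
| 1.5 | 1.64 | 0.292 | 0.248 |
| 2.0 | 1.53 | 0.293 | 0.230 |

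The model standard error stays near 0.29 while the true one falls, so the stated error is too large.

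**Check 3: the planned tertile analysis, simulated** (100 pairs, 300 runs per setting). Log EDC = b × matching score + unit noise, so the within-pair correlation among unaffected women is b²/(1 + b²): 0.25/1.25 = 0.2 at b = 0.5, and 1/2 = 0.5 at b = 1. Median odds ratio, third versus first tertile, true value 2:

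| b | Crude | Unconditional with matching score | Conditional |
|---|---|---|---|
| 0 | 2.05 | 2.06 | 2.06 |
| 0.5 | 1.79 | 1.97 | 1.99 |
| 1.0 | 1.53 | 2.01 | 2.10 |

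Power was 36% crude against 42% adjusted at b = 0.5, and 19% against 36% at b = 1. With a true odds ratio of 1, the crude test rejected in 5.3%, 2.7% and 1.7% of runs at b = 0, 0.5 and 1. With 300 runs the Monte Carlo error is up to √(0.42 × 0.58/300) = 2.8 percentage points for power. Coverage of the crude 95% interval at a true value of 2 stayed at 93% to 94%, because the oversized standard error offsets the bias. The loss therefore shows in the point estimate and the power.

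**Check 4: an unpaired comparison of a continuous measure.** The unpaired test assumes variance 2/n per squared SD; the true variance is 2(1 − ρ)/n. The actual type I error is 2[1 − Φ(1.96/√(1 − ρ))]: 3.9%, 1.9% and 0.6% at ρ = 0.1, 0.3 and 0.5. For a difference of 0.40 SD with n = 100 and ρ = 0.3:

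- assumed SE = √(2/100) = 0.141; true SE = √(1.4/100) = 0.118
- unpaired power = Φ((0.40 − 1.96 × 0.141)/0.118) = 85%
- paired power = Φ(0.40/0.118 − 1.96) = 92%

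This is a normal approximation and serves only as a guide to Mann-Whitney U.

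**The case against.** The strongest reply is that this is silence rather than error. The term logistic regression does not exclude a conditional or adjusted model, and a journal article may leave model terms to the full protocol or analysis plan. The list of reproductive and lifestyle variables appears under a heading that calls them covariables, and the Discussion says that the questionnaires are meant to help control modifiable factors. That reply stands for the choice of confounders: a reader might infer that parity, hormone use or smoking will go uncontrolled, but the article does not say so.

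The reply is weaker on the matching. The same section is specific about imputation, variance checks, software, thresholds and tertile cut-points, and it states adjustment for the linear models but not for the odds ratios. Mann-Whitney U is a positive choice of an independent-samples test.

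Three further limits stand:

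- **Size.** A within-pair correlation of 0.5 for a binary exposure at 50% prevalence corresponds to a latent correlation of about 0.71 (sin(π × 0.5/2)), a great deal for age, BMI category and hospital to explain. At 0.1 the shift is ln(2/1.87) = 0.07 on the log scale, small beside a standard error of about 0.29. Creatinine adjustment may also weaken any link with BMI.
- **Pairing.** It is inferred. If the pairs are not retained, paired methods are not available.
- **The t-test.** A reader might count it as another analysis that ignores the matching. The article describes it as a comparison of intestinal with mammary microbiota and for each metabolite, and names no case-control contrast.

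**Conclusion.** The point holds in conditional form. The design is matched, and the stated odds-ratio model and microbe test do not use the matching. Followed as written, the odds ratios will be attenuated and the tests conservative wherever age, BMI category or hospital is related to the measurement.

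It is tempting to say outright that the odds ratios are biased and the standard errors wrong. The document does not support that: there is no bias if the factors are unrelated to exposure or if the true odds ratio is 1, and nothing in the article fixes the correlation. Across the assumed values a true odds ratio of 2 appears as about 1.4 to 2.0, with the low end needing a strong link. Nor does the article allow a statement about the net direction once other confounding is considered, since that can act either way. The error does not inflate false positives; its cost is understated associations and lost power in a study of about 100 pairs.

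**What to change.** - **Odds ratios:** state conditional logistic regression on the matched pair. If pairs are not retained, or are broken by missing samples, use unconditional logistic regression that includes age, BMI category and hospital. In Check 3 both recovered the true value closely.
- **Case-control comparisons of microbes:** use a paired test (signed-rank), or a model containing the matching factors.
- **PERMANOVA:** where it compares cases with controls, restrict permutations to within pairs, or stratify them by the matching factors if pairs are not kept.
- **Matching:** say whether it is one-to-one and whether pair identity is recorded.

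The cost is analysis wording only. The matching variables are already collected, and the article reports that enrolment continues. The one downside is that pairs with a missing member or sample drop out of the conditional analysis; the unconditional model with the matching factors avoids this.
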